## Abstract

**Background:**

Heart failure is likely to be particularly prevalent in the nursing home population, but reliable data about the prevalence of heart failure in nursing homes are lacking. Therefore the aims of this study are to investigate (a) the prevalence and management of heart failure in nursing home residents and (b) the relation between heart failure and care dependency as well as heart failure and quality of life in nursing home residents.

**Methods/design:**

Nursing home residents in the southern part of the Netherlands, aged over 65 years and receiving long-term somatic or psychogeriatric care will be included in the study. A panel of two cardiologists and a geriatrician will diagnose heart failure based on data collected from actual clinical examinations (including history, physical examination, ECG, cardiac markers and echocardiography), patient records and questionnaires. Care dependency will be measured using the Care Dependency Scale. To measure the quality of life of the participating residents, the Qualidem will be used for psychogeriatric residents and the SF-12 and VAS for somatic residents.

**Conclusion:**

The study will provide an insight into the actual prevalence and management of heart failure in nursing home residents as well as their quality of life and care dependency.

**Trial registration:**

Dutch trial register NTR2663

## Background

Heart failure (HF) is a highly prevalent chronic disease in older persons. Its prevalence increases with age reaching 15–20% in those aged over 80 years [1]. According to current guidelines [2], HF is stated as a clinical syndrome characterized by the presence of symptoms and typical signs of HF and objective evidence of a structural and/or functional abnormality of the heart, usually illustrated by echocardiography [2]. Accurate diagnosis of the presence and aetiology of HF is important given its crucial influence on therapy. However, signs and symptoms of HF in older persons are often obscured, due to physical limitations or the unreliability of clinical history due to dementia [3]. In addition, signs of HF, such as fatigue or dyspnoea, are often attributed to the normal ageing process. Besides, symptoms are often non-specific and can be attributed to other common diseases in older persons such as venous insufficiency or obesity [4]. The diagnosis of HF is especially challenging if co-morbidities are present that share common symptoms of HF are present such as COPD and venous insufficiency [5].

This implicates that the diagnosis of HF is particularly difficult in older persons and nursing home residents. The latter represent a specific group, involving very frail and disabled elderly persons with chronic somatic diseases or progressive dementia, both often being complicated by co-morbidities [6]. The prevalence of HF in nursing home residents is estimated to be 20–25% [3,7]. Furthermore, HF in this specific group is likely to be underdiagnosed, due to the lack of knowledge regarding adequate diagnosis and treatment of HF in this population. This counts the more because nursing home residents are often excluded from clinical and epidemiological studies.

It is well known that HF is accompanied by a high patient and economic burden [8]. HF patients are often re-admitted to hospital, mainly due to periodic episodes of clinical deterioration [9]. In the Netherlands, as well as other Western countries cardiovascular diseases (including HF) account for the highest hospitalisation rate, resulting in high financial costs [10,11].

Notwithstanding the fact that survival of HF has improved in recent decades, once hospitalised for heart failure, 33% of elderly patients die within the following year [12]. Women and older persons experience less improvement in survival, partly because they often suffer from HF with a preserved ejection fraction, but also because they are less likely to receive treatment with B-blockers and ACE-inhibitors [12,13].

HF also leads to an impaired quality of life [14,15]. The symptoms of HF such as fatigue and dyspnoea result in increased care dependency which is accompanied by a decline in health status and quality of life [16]. Therefore, early diagnosis and treatment of HF may prevent the progression of heart failure and lead to improvement in symptoms and quality of life [17]. Furthermore, it is known that older persons are less likely to receive evidence-based treatments for HF [18]. Although ACE- inhibitors have been demonstrated to benefit HF patients, they remain underused for HF treatment in nursing home settings [19].

The aim of this study is to gain an insight into the prevalence and management of HF in nursing home residents and to explore the association between HF, care dependency and quality of life.

The following research questions will be addressed:

1.What is the prevalence of HF in Dutch nursing home residents?

2. How is HF currently treated in nursing home residents both pharmacologically and non-pharmacologically?

3. What is the association between HF and the care dependency and quality of life of nursing home residents?

This article describes the study protocol.

## Methods/design

This multicentre study will follow a cross-sectional design.

### Setting

Five healthcare organisations that provide institutional long-term care in the Southern part of the Netherlands will participate in the study. These healthcare organisations have various nursing home facilities for both chronic somatic and psychogeriatric care. Dutch nursing home care is provided by teams of registered nurses, nurse assistants, paramedical professionals and nursing home physicians, who are employed by the nursing homes themselves. The care can be characterised as continuing, long lasting, systematic and multidisciplinary care (CLSM) that is provided via an integrated care plan after a thorough and integral assessment of the resident’s problems. Nursing homes also have a geriatric rehabilitation function for a substantial number of somatic residents. The nursing home physician is responsible for all medical care and initiates the different therapeutic interventions [20].

### Study population and sample

The study population will consist of nursing home residents who receive long term care on somatic or psychogeriatric wards. Both somatic and psychogeriatric residents will be eligible when over 65 years of age. Residents receiving palliative care or admitted for short-term rehabilitation ( staying < 2 months) will be excluded. The overall number of nursing home residents at the five participating healthcare organisations is about 4500. After excluding the places allocated for rehabilitation and terminal care about 3500 residents will be available for recruitment.

A total of 1000 nursing home residents will be included in the study, with 200 from each participating organisation. Based on the current segmentation of somatic residents (35%) versus psychogeriatric (65%) residents in Dutch nursing homes, we aim to include 70 somatic and 130 psychogeriatric residents from each organisation.

In a feasibility study on somatic wards, we found that about 50% of the approached residents were willing to participate. Reasons given for not participating included: they considered themselves too old, or believed that the investigations would be too burdensome. We also encountered difficulties, when asking legal representatives to make decisions regarding participation on behalf of residents. These preliminary findings were in line with a study conducted by Barnes et al, who also focused on the recruitment of older people in a HF study, in which only 30% of the initially identified participants agreed to participate [21].

Therefore, it will probably be necessary to approach three times the number of residents per healthcare organisation in order to recruit 200 residents per site.

#### Sample size calculation

The calculation of sample size was based on an estimated prevalence of HF in nursing home residents of *p* = 0.20 with a standard deviation of 0.025 and a confidence level (%) of 95%. No power considerations are required, because there is no null hypothesis to be tested. Accordingly, 983 residents should be included in the study; therefore a sample of 1000 residents will be selected.

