### Statistical analysis

The data will be analysed using SPSS software PASW Statistics 17 and will include descriptive frequency distributions for all variables. Differences between groups will be tested using Student’s T-test or analysis of variance (ANOVA) for continuous (dependent) variables and the Chi-square test (cross-table analysis) and/or multivariable logistic regression analyses for discrete (dependent) variables.

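### The sample size of 983 assumes a simple random sample, so 1000 residents nested in facilities will not give the implied ±2.5-point precision on prevalence

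*Protocol article*

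**What the plan says.** Under Sample size calculation, the article takes an "estimated prevalence of HF in nursing home residents of *p* = 0.20" "with a standard deviation of 0.025 and a confidence level (%) of 95", and arrives at the target: "983 residents should be included in the study; therefore a sample of 1000 residents will be selected". It mentions no design effect, intracluster correlation or other allowance for clustering.

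The sampling structure is described elsewhere. Under Study population and sample: "A total of 1000 nursing home residents will be included in the study, with 200 from each participating organisation". Under Setting: "These healthcare organisations have various nursing home facilities for both chronic somatic and psychogeriatric care". Selection of participants adds that, within each organisation, the facilities with the most residents are approached first. The first research question, in Background, asks about prevalence in Dutch nursing home residents generally.

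Under Statistical analysis: "Differences between groups will be tested using Student’s T-test or analysis of variance (ANOVA) for continuous (dependent) variables". For discrete outcomes it names the chi-square test and multivariable logistic regression. No term for facility or organisation is mentioned, and no method is given for the prevalence confidence interval.

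**The concern.** A formula for independent residents has been applied to a sample drawn from a limited number of facilities. Facilities differ in case-mix. The Setting section makes the nursing home's own physician responsible for medical care and for starting treatment, so treatment patterns in particular can be expected to be alike within a facility. Because the research question concerns Dutch nursing home residents, differences between facilities are sampling error for that target, and the formula leaves them out.

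At stake is the headline result. Prevalence is the first research question and the only basis for the sample size. If residents in the same facility resemble each other, the study is less precise than its sample size implies. An interval computed under independence would also cover the true value less often than 95% of the time.

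**Working it through.** **Inputs from the article:** p = 0.20; d = 0.025; 95% confidence (z = 1.96); n = 1000; five organisations of 200; about 3500 residents available.

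**Inputs not in the article (assumed):** participants per facility, m; intracluster correlation, ICC. With 200 per organisation, m = 50 means 200/50 = 4 facilities per organisation (20 in all), and m = 25 means 8 (40 in all).

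**Step 1: reproduce 983.** n = z²p(1−p)/d² = 1.96² × 0.20 × 0.80 / 0.025² = 983.4. This matches. Other readings do not:

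- 0.025 as a standard error: 0.16/0.025² = 256
- one-sided 95%: 693
- with a finite population correction: 768 (population 3500) or 807 (population 4500)

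So 0.025 acts as the half-width of a two-sided 95% interval, and the design effect (DE) is 1.

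**Step 2: the slack in rounding up.** 1000/983.4 = 1.017, so the extra 17 residents cover a design effect of about 1.02. Setting 1 + (m−1) × ICC = 1.017, that margin is used up at an ICC of 0.017/24 = 0.0007 for m = 25, or 0.017/49 = 0.0003 for m = 50.

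**Step 3: precision at n = 1000 with clustering.** DE = 1 + (m−1) × ICC; half-width = 1.96 × √(0.16 × DE/1000); effective n = 1000/DE.

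| m | ICC | DE | Effective n | Half-width (points) |
|---|---|---|---|---|
| any | 0 | 1.00 | 1000 | 2.5 |
| 25 | 0.01 | 1.24 | 806 | 2.8 |
| 25 | 0.02 | 1.48 | 676 | 3.0 |
| 25 | 0.05 | 2.20 | 455 | 3.7 |
| 50 | 0.01 | 1.49 | 671 | 3.0 |
| 50 | 0.02 | 1.98 | 505 | 3.5 |
| 50 | 0.05 | 3.45 | 290 | 4.6 |

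**Step 4: coverage if the interval ignored clustering.** Coverage = 2Φ(1.96/√DE) − 1. At m = 50 this is about 89% (ICC 0.01), 84% (ICC 0.02) and 71% (ICC 0.05).

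**Step 5: comparing residents with and without heart failure.** Heart failure status varies within facilities, so the relevant variance factor is roughly 1 + (m−1) × ICC(HF) × ICC(outcome). At m = 50:

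- ICCs of 0.02 and 0.05: 1 + 49 × 0.001 = 1.05, so the true standard error is √1.05 = 1.02 times the naive one
- both ICCs 0.05: 1 + 49 × 0.0025 = 1.12, a ratio of √1.12 = 1.06

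For groups defined at ward or facility level there is no such dilution, and the full design effect of Step 3 is the better guide.

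**The case against.** Several points limit the concern.

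- **The analysis may be specified elsewhere.** The Statistical analysis section is two sentences in a condensed article. It names families of tests, does not say that facility will be ignored, and gives no method for the prevalence interval. A full protocol or analysis plan could add clustered variance. This stands for the analysis, so the undercoverage figures are conditional on a naive interval. It does not help the sample size, which is stated here and reproduces only without a design effect.
- **Recruitment is not by whole facility.** A reader might infer that it is. The article describes individual or proxy consent, uptake of about 30% to 50%, and approaching three times the number needed. Participants per facility are therefore unknown and fewer than the residents living there.
- **Diagnosis is largely centralised.** A reader might infer that four physicians per site make the diagnosis cluster strongly by assessor. One expert panel makes the final diagnosis, one laboratory measures NT-proBNP, and a cardiologist or fellow records the echocardiogram. Site physicians supply history, examination and ECG reading. The fixed 70/130 somatic/psychogeriatric split also removes one difference between organisations. These features lower the plausible ICC for prevalence, but they do not remove facility case-mix or clustering of treatment.
- **A finite population correction could offset it.** For 1000 of 3500 the variance factor is 2500/3499 = 0.71, which would cancel a design effect up to 1/0.71 = 1.4. That holds only if the target were the residents of these five organisations. The research question is wider, and 983 does not use the correction.

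**Conclusion.** The point holds for the sample size and the precision it implies. The 983 contains no allowance for clustering, the design is clustered, and rounding up to 1000 leaves almost no margin. Under assumed ICCs of 0.01 to 0.05, the expected half-width is about ±2.8 to ±3.7 points at 25 participants per facility and ±3.0 to ±4.6 points at 50. Neither quantity is in the article, so these are ranges under assumptions and not estimates. With an ICC of zero nothing changes.

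A reader might go further and conclude that every planned test gives p-values that are materially too small. The documents do not support that. The tests named do assume independent residents, but this matters mainly for treatment patterns and for groups defined at ward or facility level. For residents with and without heart failure, the standard error is off by only about 2% to 6% under the values in Step 5.

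This should be fixed but does not threaten the study. The point estimate, recruitment and measurements are unaffected. Even ±4.6 points would separate the 15–20% and 45% prevalences contrasted in the Discussion.

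**What to change.** 1. Keep n = 1000.
2. Under Sample size calculation, describe 0.025 as the half-width of the 95% confidence interval.
3. State that ±2.5 points assumes independent residents. Give the expected half-width under clustering, with the assumed ICC and participants per facility beside each figure (for example, the table above).
4. Compute the prevalence interval with organisation as stratum and facility as cluster. This treats the five organisations as fixed, so variation between organisations is not in the interval; say so when generalising to Dutch nursing homes.
5. For group comparisons, use facility-robust standard errors with a small-sample correction, or a facility random intercept with organisation as a fixed effect. The correction matters because clusters are few: 20 facilities in five strata would leave 20 − 5 = 15 degrees of freedom.

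The cost is wording in two sections and recording each resident's facility. No extra residents, visits or measurements are needed. The drawback is that the stated precision becomes less favourable.

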### Selection of participants

For practical and logistic reasons, nursing home residents living in the facilities with the highest number of residents, will be the first to be recruited per care home organisation. The residents and/or their legal representatives will receive a letter describing the purpose and content of the study. Informed consent will be obtained from the residents themselves or from their legal representatives in the case of psychogeriatric residents or residents with aphasia.

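### Largest-facility-first recruitment, a fixed 200 per organisation and 50–70% expected refusal put the crude heart failure prevalence at risk of selection bias that the plan treats only as a loss of numbers

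*Protocol article*

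**What the plan says.** All references are to the Protocol article.

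- **Target.** Research question 1 (end of Background) asks for the prevalence of HF in Dutch nursing home residents. Setting names five organisations in the south of the country.
- **Order of recruitment.** Selection of participants says that "nursing home residents living in the facilities with the highest number of residents, will be the first to be recruited per care home organisation", for practical and logistic reasons. No random or consecutive selection is described.
- **Allocation.** Study population and sample fixes 200 residents per organisation (70 somatic, 130 psychogeriatric), 1,000 in all, from about 3,500 available.
- **Consent.** The same section reports: "In a feasibility study on somatic wards, we found that about 50% of the approached residents were willing to participate". Reasons for refusing were feeling too old and expecting the examinations to be a burden. It then cites an HF recruitment study "in which only 30% of the initially identified participants agreed to participate" and concludes that "it will probably be necessary to approach three times the number of residents per healthcare organisation in order to recruit 200 residents per site".
- **Precision.** Sample size calculation uses an "estimated prevalence of HF in nursing home residents of *p* = 0.20 with a standard deviation of 0.025" and concludes that "983 residents should be included in the study; therefore a sample of 1000 residents will be selected".
- **Analysis.** Statistical analysis "will include descriptive frequency distributions for all variables", plus tests between groups.
- **Limitations.** The Discussion says that refusal may leave the study with few participants. It does not say that those who refuse may differ from those who take part.

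**The concern.** The sample size rests on the formula for a simple random sample, so ±2.5 points covers random error only. The people examined will have passed three filters that are not random: the size of their facility, an allocation unrelated to the size of their organisation, and their own or their representative's consent.

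The consent filter matters most, because the article itself supplies a link. Some residents refused because they felt too old, and the Background says that HF prevalence rises with age. If older residents are under-represented, a crude percentage describes a younger group than the one the question is about. Enrolling the full 1,000 does not cure this, so recording refusal only as a threat to numbers names the wrong limitation for a prevalence study.

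At stake is the main result: a figure with a narrow interval that may be off by as much as that interval's half-width, and that is worded for a country although it comes from five organisations in one region.

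**Working it through.** **1. The plan's own figure.** Inputs from Sample size calculation: p = 0.20, d = 0.025, 95% confidence.

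n = 1.96² × 0.20 × 0.80 / 0.025² = 983.4, which reproduces 983. The 0.025 is called a standard deviation, but it gives 983 only as the half-width of the interval; read as a standard error it would give 0.16 / 0.025² = 256. The margin to compare any bias with is therefore ±2.5 points.

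**2. Refusal.** Bias = (1 − r) × D, where r is the consent rate and D is the prevalence in participants minus that in refusers. The article gives r (about 50% and 30%) but not D, so D is an assumption shown over a range.

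| Assumed D (points, either sign) | Bias at 50% consent | Bias at 30% consent |
|---|---|---|
| 0 | 0 | 0 |
| 5 | 2.5 | 3.5 |
| 10 | 5.0 | 7.0 |

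The bias equals the margin when D = 2.5/0.5 = 5.0 points at 50% consent, or 2.5/0.7 = 3.6 points at 30%.

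The same can be put in terms of consent by HF status, with true prevalence 20% and again with assumed rates:

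- 25% with HF, 35% without: 0.05 / (0.05 + 0.28) = 15.2%, a bias of −4.8 points.
- 30% with HF, 35% without: 0.06 / (0.06 + 0.28) = 17.6%, a bias of −2.4 points.
- 35% with HF, 25% without: 0.07 / (0.07 + 0.20) = 25.9%, a bias of +5.9 points.

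**3. Largest facilities first.** Bias = share never approached × difference in prevalence between facilities reached and not reached. I assume that recruitment stops once 200 per organisation is met; the article implies this but does not state it. The 10-point difference is also assumed.

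- 50% consent: 1,000/0.50 = 2,000 approached, 43% of 3,500 never reached, bias 4.3 points.
- Three times the target: 3,000 approached, 14% never reached, bias 1.4 points.
- 30% consent: 1,000/0.30 = 3,333 approached, 5% never reached, bias 0.5 points.

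Facility order and refusal therefore partly trade off: where refusal is worst, order hardly matters.

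**4. Fixed 200 per organisation.** Bias is zero if the organisations are equal in size or equal in prevalence. The article gives neither. With assumed sizes 1,200, 900, 600, 500 and 300 (total 3,500) and prevalences of 15, 17.5, 20, 22.5 and 25%, the equal-allocation figure is 20.0% and the size-weighted one 645/3,500 = 18.4%. With the prevalences in reverse order the weighted figure is 755/3,500 = 21.6%.

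**5. The approach factor.** Three times 200 is 600 per organisation, which yields 200 at 200/600 = 33.3% consent.

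- At 30%: 600 × 0.30 = 180 per organisation, 900 in all. Half-width 1.96 × √(0.16/900) = 2.6 points. Reaching 200 needs 200/0.30 = 667 approaches, a factor of 3.33.
- At 50%: 400 approaches suffice, a factor of 2.
- At 50% somatic and 30% psychogeriatric: 70/0.50 + 130/0.30 = 140 + 433 = 573, within 600. Under that mix, 600 falls short only if psychogeriatric consent is below 130/460 = 28.3%.

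**The case against.** A reader might infer that the crude percentage is biased, and biased downwards by nearly 5 points. The documents do not support that. Bias needs prevalence to differ by consent status, facility size or organisation, and the article reports none of these. The consent splits above are assumed, and reversing one changes the sign. The age link makes understatement plausible; it does not establish it.

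Other points in the plan's favour stand:

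- The 70/130 quota already holds the ward mix at the stated 35/65 split if it is met. A psychogeriatric shortfall is possible but not shown.
- The largest facilities come first, not exclusively. With on-site examinations including mobile echocardiography, that is a disclosed practical choice.
- The factor of three might be read as an error. It is hedged, lies between the factors implied by the two cited rates (2 and 3.33), and estimates effort rather than capping it. The two rates may not share a denominator: one is of residents approached, the other of people initially identified.
- Descriptive frequencies are not stated to be the only analysis. Weighting may sit in an analysis plan that is not shown, so its absence from an article is not an error.

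A further objection limits the remedy: post-stratification removes only the selection explained by the variables used. Refusal driven by HF itself within an age, sex and organisation stratum stays in the estimate.

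None of this answers what the article does state: refusal related to age, HF related to age, refusal discussed only as a loss of numbers, and a national question put to five regional organisations.

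**Conclusion.** The point holds as a risk, not as demonstrated bias. The selection scheme exposes the crude pooled prevalence to selection bias of unknown size and direction. It would equal the ±2.5-point margin if participants and refusers differed by about 4 to 5 points in prevalence over the cited consent range, and it is zero if they do not differ. Refusal is the main route. Facility order matters mainly if consent is nearer 50%, and the fixed 200 only if organisations differ in both size and prevalence.

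The approach factor is a minor matter. If 30% is the planning rate and only 600 per organisation are approached, the expected total is 900 rather than the required 983, and the margin widens from ±2.5 to ±2.6 points.

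This is worth changing because the age-related part can be reduced cheaply. It does not invalidate the study.

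**What to change.** 1. Report the crude prevalence together with an estimate post-stratified to the roughly 3,500 eligible residents by organisation, age band and sex, using the organisations' aggregate counts. Add ward type if the 70/130 quota is missed. Merge sparse cells.
2. State in the Discussion that refusal may bias the prevalence as well as reduce numbers, and that weighting does not remove refusal driven by HF within strata.
3. Word the conclusion as prevalence in the five southern organisations, not in Dutch nursing home residents generally.
4. State the consent rate behind the approach factor. Either give 33% for a factor of 3 or, if 30% is the planning rate, restate it as 3.33 (667 per organisation, about 3,333 of the 3,500 available, 95%). The alternative is to state an expected 900 residents and ±2.6 points.

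**Cost.** Items 2 to 4 are wording. Item 1 needs one table of counts from each organisation and gives a slightly wider confidence interval because the weights are unequal. Taking facilities in random order within organisations is optional: it would reduce the facility-size component, at some logistic cost, and gains little if nearly all residents have to be approached anyway.
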